#### Exploratory analyses

##### Sensitivity analyses

For all analyses using the Cox proportional hazards model, the assumption of independence of the distribution of time to healing/recurrence and time to other events, that is, amputation and death will be assessed and alternative models considered if there are sufficient competing risks.

A multivariable Cox proportional hazards regression model will be fitted to explore risk factors predictive of time to healing.

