#### Phase III primary objective

To determine whether one treatment strategy continued from phase II, as an adjunct to TAU, reduces time to healing of the index ulcer compared with TAU alone.

The primary endpoint is time *to healing of the index ulcer* from randomisation to the date the index ulcer is confirmed as healed at the first confirmation visit conducted by the blinded assessor (providing the index ulcer is confirmed as healed at a second clinical assessment 2 weeks later).

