#### Phase III secondary objectives

To compare one treatment strategy as an adjunct to TAU, continued from phase II, with TAU alone for:

Healing status of the index ulcer at 12, 20 and 52 weeks.Rate of ulcer infection in the foot of the index ulcer over 52 weeks post randomisation.Incidence of reulceration following healing of index ulcer over 52 weeks post randomisation.Quality of life using the Diabetic Foot Ulcer Scale—Short Form (DFS-SF) and the Five-level five-dimension EuroQol (EQ-5D-5L) over 52 weeks post randomisation.Incidence of AEs (including amputation, infection in any ulcer on the foot of the index ulcer and hospital admission) over 52 weeks post randomisation.Cost effectiveness over 52 weeks.

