### Sample size

The planned maximum sample size is 447 participants, 245 participants in phase II and 202 participants in phase III. The apportionment of participants to phase II and phase III was estimated using a series of simulation studies.

In phase II, 49 participants per treatment strategy arm and 98 participants in the TAU arm will be recruited. The target effect size in phase II is an absolute increase of 25% in the proportion of participants achieving at least a 50% reduction in wound area by 4 weeks post randomisation, assuming 39% reach at least a 50% reduction by week 4 in the TAU arm (local audit data) and 64% achieve this outcome in the treatment strategy arms.

An additional 101 participants will be recruited into each arm evaluated in phase III, corresponding to a total (phase II and III combined) of 150 in the remaining treatment strategy group and 199 in the TAU arm (total of 349 participants for evaluation in phase III).

The minimum clinically important effect size in phase III is a hazard ratio (HR) of 1.5, assuming a median time to healing of 21 weeks for the TAU arm (local audit data) and 14 weeks for the treatment strategy arms^18 27–30^ and 18.0% and 7.6% *un*healed at 52 weeks in the TAU and treatment strategy groups, respectively (assuming exponential distribution for time to healing).

Several scenarios for the power of the trial have been considered. In all cases a 10% loss to follow-up by 4 weeks and 25% loss to follow-up by 52 weeks is assumed. In the case where there is a single effective treatment strategy arm, the design has 83.9% power to recommend a truly effective treatment strategy (ie, for it to progress from phase II and for a significant result found at phase III). A treatment strategy group that progresses to phase III and which is significantly better than TAU at the two-sided 4% significance level (to control the familywise error rate at 5%) on the time to healing endpoint will be declared clinically effective.

A formal sample size review will be conducted at 52 weeks, after 220 participants have been recruited, to re-estimate the proportion of participants lost to follow-up by 52 weeks post randomisation and the final sample size. The review will allow the overall loss to follow-up to be estimated to a minimum precision ±5.7% (corresponding to half width of the 95% CI), assuming a maximum loss to follow-up of 25%.

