#### Phase III primary endpoint analysis

##### Primary analysis

The hazard ratios for the phase III endpoint will be estimated using Cox proportional hazards regression with covariates for the minimisation factors, treatment arm (fixed effects) and centre (random effects) and stratification for the phase in which the participant was recruited.

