#### Phase III secondary endpoint analysis

Similar regression-based analyses will be used for other secondary endpoints. Cumulative incidence of healing at 12, 20 and 52 weeks post randomisation will be obtained from the primary endpoint analysis model. A Poisson-Gamma regression model will be fitted to infection status over time. A Cox proportional hazards regression model will be fitted to time to reulceration of the index ulcer on those participants where healing of the index ulcer is confirmed. A repeated measures, random coefficients, linear regression model will be fitted to the DFS-SF Score over time.

All AEs and SAEs, including amputations and admissions to hospital, will be recorded and summarised by treatment strategy received. Expected treatment-related AEs include: pain, bleeding and infection from HD; bleeding, infection and skin irritation/breakdown from NPWT; seroma and allergic reaction from DCD.

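### The competing-risk analysis of healing depends on an unspecified trigger and an independence check the data cannot support, while cumulative healing is taken from the Cox model

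*Protocol article*

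**What the plan says.** The phase III endpoint (Phase III primary objective) is the time "from randomisation to the date the index ulcer is confirmed as healed at the first confirmation visit conducted by the blinded assessor", provided that a second assessment two weeks later agrees. Under Phase III primary endpoint analysis, "The hazard ratios for the phase III endpoint will be estimated using Cox proportional hazards regression", with the minimisation factors and treatment as fixed effects, centre as a random effect, and stratification by recruitment phase. Neither section says how a participant who dies, or whose index ulcer is amputated, enters the analysis.

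The one place that deals with this is Sensitivity analyses, under Exploratory analyses. For every Cox analysis, the text promises that "the assumption of independence of the distribution of time to healing/recurrence and time to other events, that is, amputation and death will be assessed". On what would follow from that check, it offers only this: "alternative models considered if there are sufficient competing risks". It gives no method of assessment, threshold or alternative model.

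For healing status, a listed secondary objective, Phase III secondary endpoint analysis states: "Cumulative incidence of healing at 12, 20 and 52 weeks post randomisation will be obtained from the primary endpoint analysis model".

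Amputation otherwise appears only as a safety outcome. The secondary objectives list "Incidence of AEs (including amputation, infection in any ulcer on the foot of the index ulcer and hospital admission", and the analysis section summarises adverse events by treatment received.

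**The concern.** There are three linked difficulties.

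- **The independence check cannot work.** A participant who is amputated or dies first never shows a healing time, and one who heals first contributes nothing on what would have happened unhealed. Dependent and independent underlying times can produce the same observed data. The article's own background also makes independence unlikely: the Introduction says that delayed healing raises the probability of amputation, and Choice of endpoints ties infection to both delayed healing and major amputation.
- **The trigger is open.** Nothing says how many competing events are enough, or what would then be fitted.
- **Cumulative incidence comes from the wrong quantity.** A Cox model that censors competing events gives the healing expected if nobody were amputated or died. That is always at least as high as the proportion who actually heal.

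At stake are the interpretation of the primary hazard ratio and the healing percentages at 12, 20 and 52 weeks that will be quoted from the trial.

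**Working it through.** **Inputs from the protocol (Sample size).** On the effect size: "The minimum clinically important effect size in phase III is a hazard ratio (HR) of 1.5". On the medians: "assuming a median time to healing of 21 weeks for the TAU arm (local audit data) and 14 weeks for the treatment strategy arms". The other inputs are exponential healing times, 150 v 199 participants, two-sided 4% significance, and loss to follow-up of 10% by week 4 and 25% by week 52. Rates of amputation and death by arm are not given, so every such rate below is assumed. For scale, the Introduction says that more than 50% of ulcers become infected and that 20% of infections lead to amputation: 0.5 × 0.2 = about 10%. That figure is for diabetic foot ulcers in general, not this trial's population.

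**Step 1: the plan's own figures.**
- Unhealed at week 52: 2^(−52/21) = 18.0% and 2^(−52/14) = 7.6%. Hazard ratio: 21/14 = 1.5. Both agree with the protocol.
- Passing phase II: Φ(0.15/√(0.64×0.36/44 + 0.39×0.61/88)) = 0.954.
- Phase III: about 261 healing events after the stated losses (piecewise exponential) give power 0.882.
- Product: 0.842, against the stated 83.9%. The design therefore reproduces with loss to follow-up alone and no separate allowance for amputation or death.

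**Step 2: cumulative incidence, equal and independent competing risk.** Let l = ln2/21 = 0.03301 (TAU) or ln2/14 = 0.04951 (strategy) per week, and m = −ln(1−q)/52, where q is the week-52 risk of amputation or death in the absence of healing. With censoring, the Cox-derived figure is 1 − exp(−l·t). The proportion who actually heal is l/(l+m) × (1 − exp(−(l+m)·t)).

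| Week 52 | TAU healed | Strategy healed | Difference |
|---|---|---|---|
| Cox-derived | 82.0% | 92.4% | 10.4 points |
| q = 5% (m = 0.000986) | 80.5% | 91.0% | 10.4 points |
| q = 15% (m = 0.003125) | 77.4% | 88.0% | 10.6 points |

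Amputation or death before healing is then 2.4–7.3% on TAU and 1.8–5.6% on the strategy, from m/(l+m) × (1 − exp(−(l+m)·52)). The overstatement of healing is 1.4–4.6 points at week 52, 0.4–1.6 points at week 20 and 0.2–0.8 points at week 12. With equal risk in both arms, the difference between arms hardly moves.

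**Step 3: hazard ratio, unequal and informative losses.** Assume that 30% are poor healers (healing hazard 0.005 per week) and the rest heal at 0.06 per week, identically in both arms. Amputation or death strikes poor healers only, at hazard m. The proportion lost by week 52 is 0.3·m/(0.005+m) × (1 − exp(−(0.005+m)·52)). The proportion healed is 0.3·0.005/(0.005+m) × (1 − exp(−(0.005+m)·52)) + 0.7·(1 − exp(−0.06·52)). Hazard ratios are from simulation with 400,000 per arm, with administrative censoring only.

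| Lost, strategy v TAU | m, strategy v TAU | Healed, strategy v TAU | Cox HR, losses censored | Subdistribution HR |
|---|---|---|---|---|
| 11% v 5% | 0.01020 v 0.00401 | 72.3% v 73.1% | 1.04 | 0.98 |
| 16.4% v 5.5% | 0.01804 v 0.00446 | 71.5% v 73.1% | 1.09 | 0.97 |

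The Cox hazard ratio leans towards the arm in which slightly fewer ulcers heal.

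**Step 4: effect on the 4% test.** With about 261 events, the expected z is √(261 × 150 × 199/349²) × ln HR = 8.0 × ln HR: 0.31 at 1.04 and 0.69 at 1.09, against the 2.05 required. The chance of a false favourable result rises from 2% to about 4% and about 9%, respectively.

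**The case against.** The strongest case against has four parts.

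- **This belongs in the analysis plan.** The article says that a statistical analysis plan will be signed off before any analysis. That plan could set a threshold and name a model, so it is not shown that the choice would follow sight of the data. This stands for the trigger. It does not rescue the independence check, which no further wording can make workable, or the stated source of the cumulative incidence figures.
- **The sentence is looser than a formal test.** Its explicit condition is the amount of competing risk; assessing independence might mean no more than describing events by arm. Censoring is implied, not stated. Both remarks are fair, and they are reasons to write the handling down.
- **The Cox hazard ratio is legitimate.** A cause-specific hazard ratio needs no independence to be valid as such. This stands in full: the primary model need not be replaced.
- **Amputations are visible anyway.** They are a named secondary outcome. However, they are summarised by treatment received, and apart from the healing result.

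A reader might infer that the primary analysis can declare success for an arm that loses more feet. The documents do not support this. They give no amputation or death rates by arm, and the shift found is small even under a threefold imbalance confined to poor healers (about 55% of those in the strategy arm). The illustration pools death with amputation. Open minor amputation wounds are eligible, so not every amputation ends the chance of healing.

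**Conclusion.** The point holds as a matter of prespecification and reporting. The stated handling of amputation and death rests on an assumption that the trial cannot check and on an undefined quantity of events. Taking cumulative incidence from the Cox model overstates healing whenever those events are censored.

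The sizes are moderate: 1.4 to 4.6 points at week 52 for an assumed 5–15% independent risk, less at weeks 12 and 20, and a Cox hazard ratio of about 1.04 to 1.09 with no healing benefit when losses are assumed unequal and informative. With equal risks in both arms, the difference in healing is almost unchanged. All of this rests on assumed event rates and on censoring that the protocol implies but does not state. It does not show that the primary hazard ratio is invalid or that the success rule is wrong. The change should be made, but the trial does not depend on it.

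**What to change.** In the protocol and the analysis plan:

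1. Remove the independence check and the condition on the amount of competing risk.
2. State how death and amputation enter the healing analysis, and define which amputations count as competing events, given that open minor amputation wounds are eligible.
3. Describe the primary Cox hazard ratio as cause-specific.
4. Always report beside it, by randomised arm, a Fine-Gray subdistribution hazard ratio for healing, with weighting for loss to follow-up, and the cause-specific hazard ratio for amputation or death. Keep the covariates and phase strata, and say how centre, a random effect in the Cox model, is handled in the Fine-Gray fit.
5. Take cumulative incidence of healing at 12, 20 and 52 weeks from the Aalen-Johansen estimator or the competing-risk model, not from the Cox model alone.

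Leave the 4% success rule unchanged. Requiring the subdistribution hazard ratio to agree in direction would add a second success condition, and the 83.9% power was not calculated for it.

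The cost is wording and one extra model; amputations are already recorded as adverse events, and deaths are expected to be captured through the same reporting. The downside is that a slightly less favourable healing estimate is always shown. For example, at a true cause-specific hazard ratio of 1.5 with an assumed 10% amputation or death before healing in both arms, the subdistribution hazard ratio is about 1.38.

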### Economic evaluation

A within-trial economic evaluation will be undertaken at week 52 post randomisation. The proposed secondary endpoints and methods for the economic evaluation follow the reference case set out by NICE.^32^ The primary economic analysis will be a cost-utility analysis presenting incremental cost-effectiveness ratios (ICERs) for each treatment strategy in rank order of effectiveness, with effects expressed in terms of quality-adjusted life years (QALYs). An NHS and Personal Social Services perspective for costs will be adopted. Costs and effects for each treatment strategy will be calculated for the trial follow-up period of 52 weeks.

Health resource use questionnaires will collect information on NHS and personal social care use in line with NICE guidelines.^32^ This will include primary, secondary and community resource use. Unit cost data will be obtained from national databases such as the *British National Formulary* and *Personal Social Services Research Unit Costs of Health and Social Care*.

Treatment costs include the cost of delivering each strategy (mainly given by person-time of healthcare professionals) and the cost of the necessary equipment. The scope of resources considered includes the direct healthcare costs incurred for necessary patient care and excludes resources driven by the study protocol (eg, routine clinics will be included, while research visits that are just for checking for reulceration are excluded; also, the cost of photography and visit time for collecting data for study purposes will be excluded). To cost the treatment strategies, data on average duration of appointments for delivering the treatment strategy will be collected.

ICERs, incremental net monetary benefit and incremental net health benefit statistics will be computed. NICE considers a cost per QALY within the range of £20 000–£30 000 to be acceptable.^32^

Multiple imputation will be used to address any issues of missing data in the base case analysis on the assumption of MAR. Complete case analysis will be conducted as a sensitivity analysis.

Probabilistic sensitivity analysis will be used to assess the impact of sampling uncertainty on the within-trial evaluation results. Simulated cost and QALY estimates will be plotted on the cost-effectiveness plane to illustrate the uncertainty surrounding cost-effectiveness estimates^33^ and presented as cost-effectiveness acceptability frontier to capture the varying probability of interventions being the most cost-effective over a range of willingness to pay for QALY thresholds.^34^

In addition, alternative scenarios will be explored in the sensitivity analysis to test the robustness of the main trial analysis results.

### Data management

Data will be monitored for quality and completeness and missing data will be chased up. Data received, including photographs will be stored in a secure database at Leeds CTRU in accordance with the 2018 Data Protection Act and the General Data Protection Regulation.

### Patient and public involvement

The trial was supported at the stage of developing the grant application by the Sheffield Teaching Hospitals Lay Advisory Panel for Diabetes & Endocrinology Research. Their input was central to study design, actively helping to shape discussions and decisions through written feedback and group discussion. In particular they informed decisions on how frequently patients should be reassessed at the study site; whether patients would be willing to report healing or other outcomes directly to the research team or through their community clinician; agreement to completion of questionnaires; wound tracing and photographs which may be considered a burden; how willing patients will be to take part in the study; the acceptability of each intervention.

The trial has two Patient and Public Involvement (PPI) representatives on the Trial Steering Committee who have provided input into the patient information sheet and other trial documentation intended for use by patients. The PPI representatives also provide input into the design and conduct of the trial at 6 monthly meetings. This high-level involvement in project management aims to ensure patients’ perspectives are fully integrated in key decisions about the trial, delivery and interpretation/dissemination of findings.

## Discussion

### MAMS design

The chosen MAMS design provides an efficient platform for assessment of several competing interventions, quickly homing in on the treatment strategy with greatest potential to be effective, early dropping of ineffective treatments and allowing assessment of combinations of treatments.^20 35–37^ Specific advantages of the MAMS design include comparing multiple treatment arms to a shared control group thereby requiring fewer patients, improved consent/recruitment rates since patients are more likely to receive an active treatment^37^ and common eligibility criteria across trial arms.^20^ Moreover, recruitment to all treatment strategies will continue during analysis and reporting of phase II data to ensure no loss of momentum in recruitment at sites.

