**Figure 1 F1:**
[figure not shown]
Multiple Interventions for Diabetic Foot Ulcer Treatment Trial (MIDFUT) design.

Three treatment strategies will be compared with TAU in phase II. Treatment strategies for which the estimated proportion of responders is less than 10% higher than the proportion of responders on TAU (absolute difference) will be dropped at the end of phase II (response defined as achieving at least 50% reduction in wound area of the index ulcer). One treatment strategy and TAU will be evaluated in phase III. If more than one treatment strategy shows a sufficient response in phase II, then the decision on which treatment strategy to evaluate in phase III will consider information on the safety profile and costs of the treatment strategies up to 4 weeks post randomisation.

A maximum of 447 participants will be recruited, 245 participants in phase II and at most 202 participants in phase III. Recruitment at centres will continue without interruption between phase II and phase III.

All participants from phases II and III will be followed up at weeks 1, 2, 4, 8, 12, 20 and 52 post randomisation (including those where healing of the index ulcer has been confirmed), or week 54 where healing of the index ulcer is first reported at week 52 (see figure 2).

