### Randomisation

Following confirmation of eligibility, consent and completion of baseline assessments, participants will be randomised. In phase II, randomisation will be in a 1:1:1:2 allocation ratio to the three treatment strategies and TAU group, respectively, as an approximation to Dunnett’s recommendation.^22^ In phase III, randomisation will be in a 1:1 allocation ratio to one treatment strategy and TAU. Randomisation in both phases will use a minimisation algorithm, incorporating a random element, via a central 24 hours automated telephone or internet randomisation system, based at the Leeds Clinical Trials Research Unit (CTRU). The dynamic allocation method will ensure the groups are well balanced for:

Centre.Aetiology (neuropathic or neuro-ischaemic).Index ulcer duration (<6 months, ≥6 months).Anatomical site (forefoot, midfoot/hindfoot).Presentation (DFU, surgical debridement wound, open minor amputation).

In addition, at the time of randomisation, 25% of participants will be randomly selected to have photographs of the index ulcer taken, if it is unhealed, at weeks 12, 20 and 52, for central blinded review.

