### Statistical analysis

A statistical analysis plan for phase II and phase III final analyses will be finalised and signed off before any data analyses are conducted.

The complete case population will be used for the analysis of the phase II endpoint under the assumption that data are missing at random (MAR).^31^ A sensitivity analysis will be considered if there is differential missing endpoint data observed across treatment arms.

Phase III analyses will use intention to treat whereby participants will be analysed according to randomised treatment group. A per-protocol population will also be defined.

For phase III endpoint analyses, data from all participants recruited in phase II and phase III will be included.

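### With all strategies recruiting while phase II is analysed, a maximum of 447, 101 extra per continuing arm and 349 in phase III cannot all hold

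*Protocol article*

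**What the plan says.** Phase II: the Sample size section states that "49 participants per treatment strategy arm and 98 participants in the TAU arm will be recruited", and Randomisation states that "randomisation will be in a 1:1:1:2 allocation ratio to the three treatment strategies and TAU group".

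Phase III: Sample size continues, "An additional 101 participants will be recruited into each arm evaluated in phase III". This gives 150 on the selected strategy and 199 on TAU, a "total of 349 participants for evaluation in phase III". Randomisation sets the phase III ratio at 1:1.

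Ceiling: the design description in Methods, after Figure 1, says "A maximum of 447 participants will be recruited, 245 participants in phase II and at most 202 participants in phase III".

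Between the phases: the Discussion (MAMS design) says that "recruitment to all treatment strategies will continue during analysis and reporting of phase II data".

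Analysis: for phase III endpoints, "data from all participants recruited in phase II and phase III will be included" (Statistical analysis). The primary Cox model has "stratification for the phase in which the participant was recruited" (Phase III primary endpoint analysis).

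**The concern.** The phase II endpoint is read at 4 weeks. Tracings are then measured centrally, the results are analysed, and the data monitoring committee makes its recommendation to the steering committee. The gap between the 245th randomisation and the selection decision therefore cannot be empty. Everyone randomised in that gap can still be sent to any of the four arms, but the sample size leaves no room for anyone in a dropped arm beyond its first 49.

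Two things follow. First, either the stated maximum or the stated phase III size will not be delivered. Second, these overrun participants come after the phase II sample but are allocated at the phase II ratio, so the article does not settle which stratum of the Cox model they enter. Placed with phase III, they would mix 1:2 and 1:1 allocation (selected strategy to TAU) within one stratum over calendar time.

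**Working it through.** **1. The plan's counts.** 3 × 49 + 98 = 245. 245 + 2 × 101 = 447. 49 + 101 = 150 and 98 + 101 = 199, total 349. All agree as printed. The remainder, 447 − 349 = 98 = 2 × 49, is the phase II content of the two dropped arms. The set is consistent only with zero overrun.

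**2. The plan's power (83.9%, one effective strategy).** Inputs from Sample size: response 64% v 39%, 10-point progression threshold, 10% lost by week 4, hazard ratio 1.5, medians 14 and 21 weeks, 25% lost by week 52, two-sided 4% level.
- Probability that the effective arm passes and ranks top, simulated with 44 evaluable v 88: 0.949.
- Phase III events, assuming exponential healing and exponential loss: 150 × 0.848 + 199 × 0.741 ≈ 275.
- Schoenfeld: √(274.7 × (150/349) × (199/349)) × ln 1.5 − 2.054 = 1.27, so power 0.898.
- Product: 0.949 × 0.898 = 85.3%, within 2 points of the stated figure.

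Other modelling choices give 79.1% (the lost 25% contribute no events), 83.8% (response and healing linked by a copula) and 85.0–86.7% (joint log-rank simulations).

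**3. Overrun of m participants at 1:1:1:2, cap of 447 held, 1:1 afterwards.**
- Selected arm: 49 + 0.2m + (202 − m)/2 = 150 − 0.3m
- TAU: 98 + 0.4m + (202 − m)/2 = 199 − 0.1m
- Overrun in dropped arms: 0.4m
- Phase III total: 349 − 0.4m

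**4. Cap released instead, 1:1 afterwards.**
- To reach at least 150 and 199, each arm needs 101 − 0.2m more after the decision. The arms are then 150 and 199 + 0.2m, and the trial total is 447 + 0.6m.
- A maximum of 447 + 0.4m restores only the total of 349, split (150 − 0.1m) v (199 + 0.1m).

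**5. Size of m.** Trial status gives 88 randomised from 30 October 2017 to 4 December 2019, about 25.1 months: 3.5 per month. Completing 447 by 31 August 2022 needs 359 in about 32.9 months: 10.9 per month. The length of the window is not stated; 2–4 months is assumed, with 6 months as an upper case.

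| Window, rate per month | m | Selected v TAU at 447 | Phase III total | Power (from 85.3%) | Maximum if at least 150 and 199 |
|---|---|---|---|---|---|
| 2 months, 3.5 | 7 | 147.9 v 198.3 | 346.2 | 85.0% | 451 |
| 4 months, 3.5 | 14 | 145.8 v 197.6 | 343.4 | 84.7% | 455 |
| 2 months, 10.9 | 22 | 143.4 v 196.8 | 340.2 | 84.4% | 460 |
| 4 months, 10.9 | 44 | 136.8 v 194.6 | 331.4 | 83.4% | 473 |
| 6 months, 10.9 | 66 | 130.2 v 192.4 | 322.6 | 82.3% | 487 |

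The power loss is 0.3–1.9 points for 2–4 months and 3.0 points for the 6-month case (3.7 if the lost 25% contribute no events). The copula model falls from 83.8% to 82.5% at m = 22 and 81.9% at m = 44, with a Monte Carlo standard error of about 0.5 points.

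**The case against.** Every printed sum is correct; what is missing is an allowance for overrun. The power came from the trial's own simulations, which are not shown and may have modelled it. The window is an assumption, and at the observed accrual only about 3–6 participants would be lost to dropped arms. Phase II might also be analysed on fewer than 245, with the overrun falling inside that number. A sample size review is planned, and labelling participants for a stratified model is ordinary analysis-plan detail.

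Much of this limits the size of the problem but does not remove the conflict. The article does not say that phase II is analysed early, and if it were, 49 and 98 would not be the analysed sample. The review re-estimates loss to follow-up, not overrun. An analysis plan cannot reconcile a stated maximum with a stated recruitment rule.

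A reader might infer that the 83.9% power is wrong, or should be restated as about 82%. The documents support neither. The power stands if the arms are filled to 150 and 199. If the cap is held, the loss is smaller than the spread between reasonable models with no overrun at all (79.1% to 86.7%). Closeness to 83.9% in one such model is no evidence that overrun was ignored.

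On stratification, the article does not say what the phase strata are for, and nothing in it shows drift in healing over time. A separate overrun stratum is a reasonable option, not a demonstrated correction.

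**Conclusion.** The conflict holds. If one strategy progresses and anyone is randomised to a later-dropped arm after participant 245, then 447, 101 extra per arm and 349 cannot all be true. With 447 held and a 2–4 month window, the phase III comparison is about 346–343 at observed accrual and 340–331 at the accrual needed, with roughly 0.3–2 points less power (about 3 with 6 months). With the arms filled to at least 150 and 199, the power is unaffected and the maximum becomes about 447 + 0.6m, or 451–473 over the same range.

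This assumes that 1:1:1:2 applies throughout the window, because it is the only ratio the article gives for all four arms, and that 1:1 follows. The counts follow from the text; the window, the accrual during it and the power changes are illustrative. Severity is minor to moderate.

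**What to change.** Reconcile the MAMS design paragraph with the Methods design description and Sample size:

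- State what triggers the phase II analysis, the overrun expected before the decision, its allocation ratio, and how those participants are counted.
- Then choose one. Either restate the maximum (about 447 + 0.6m to secure at least 150 and 199; 447 + 0.4m secures only the total of 349), or keep 447 and restate the phase III arm sizes and power, re-run in the trial's own simulations.
- State which stratum overrun participants enter in the Cox model, preferably by the allocation ratio in force when each was randomised, so that 1:2 and 1:1 are not mixed in one stratum.

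Keeping 447 costs wording, a simulation re-run and a slightly lower stated power. Raising the maximum costs about 4–26 more participants over the 2–4 month range. With 88 of 245 randomised at the article's status date, there was time to settle this before phase II filled.
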